**1.3.6 Rationale for studying Hutterite colonies.**

**1.3.6.1 Internal validity:** The unique nature of the Hutterite population offers an important opportunity to understand whether there is an indirect benefit to immunizing children with inactivated influenza vaccine. Hutterite colonies, where members live communally on colonies of typically 80 to 120 people, are relatively isolated from towns and cities. Regular contact with outside community members is limited. However, outbreaks of influenza in Hutterite colonies occur regularly with influenza being introduced from exposure to outsiders. At the age of 36 months children begin school in a single classroom on the colony and continue until the age of 15, at which point they are considered adults. Meals are shared communally, although children and adults eat separately. Importantly, children have regular contact with those adults and others who are at high risk for complications of influenza. Thus, there is a greater likelihood of child to adult influenza transmission and less opportunity for reintroduction of influenza from non-Hutterite communities. Since the colonies are not very large, it is possible to obtain detailed demographic, health, and immunization information for all members. We recognize that there is uncertainty about the exact proportion of children that need to be immunized in order to show indirect benefit. Nevertheless, it has been estimated through modeling that for influenza strains that transmit well among children, immunization of about 70% of children may greatly reduce transmission in entire communities (22- 25). Modeling also suggests that even lower rates of vaccination may yield benefit, such that vaccinating 20% of children could reduce cases by 46% and 80% coverage would reduce rates by 90% (25). Moreover, such estimates may be conservative for the Hutterite community which has stronger contact networks. Hutterite colonies are relatively homogeneous in terms of their genetic lineage and age and sex distributions, which is of benefit for this proposed trial since it reduces the possibility of imbalances between study arms.

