
**2.11 What is the proposed sample size and what is the justification for the assumptions underlying the power calculations?** In our pilot study 8 of 57 (14%) participants had a greater than four fold rise or decline in titres (see section 1.3.7) due to either a non-vaccine strain or due to a vaccine strain in persons who were not immunized. Although previous studies that have included both viral culture and serology demonstrate that infection rates vary, an estimate of 10%is in keeping with overall community rates for years where either H3N2 or H1N1 predominate (8,9). We will test whether > 70% level of immunization can, over single influenza seasons, reduce the rate of laboratory confirmed influenza infection from 10% to 5%. If the proposed clinical trial was conducted by randomizing individuals and not clusters, 474 participants in each arm would be needed to have 80% power to detect a 50% reduction in influenza (assuming a baseline attack rate of 10%, a risk reduction of 0.50 (5%), , and type 1 error of 0.05). To adjust for the effect of within cluster dependency, a variance inflation factor is calculated using the equation 1 + (m-1), where m=average size of the cluster (per cluster=50) and = the intracluster correlation coefficient (ICC). ICCs for cluster randomized trial are seldom accurately predicted (39). Furthermore, there is little data on Hutterite colony attack rates as these are not collated by the health regions. Therefore, as recommended (39), we show in Table 3 sensitivity analysis demonstrating the power that can be achieved using a sample size of 60 clusters (the number of colonies needed to address the study question) and the range of ICCs commonly reported in cluster randomized controlled trials. We have assumed a cluster size of 50, which is the typical number of individuals in colonies interested in participating in the study. Table 3 demonstrates that with a sample size of 60 clusters we will be adequately powered to detect a difference over the range of ICCs commonly reported for cluster randomized controlled trials, 0.01 to 0.05. The table also demonstrates that our sample size allows us to assess a 50% reduction in the primary outcome assuming baseline event rates as low as 8% within a range of ICC from 0.01 to 0.04. This equates to a sample size of 1500 participants in each group. For the other comparisons that we plan to assess, sensitivity analysis shows adequate power to assess differences between study groups. For example, for testing the indirect benefit to high risk participants, for 15 high risk participants per colony, enrolling 60 colonies would give 84% power to detect a 50% reduction in laboratory-confirmed influenza (including serology which will increase the baseline event rate) from 12% to 6% between groups assuming an ICC is 0.04 and one sided alpha. The sample size has ≥ 90% power (two sided test, 60 clusters, 50 participants per cluster, ICC of 0.04) to detect the following absolute reductions: 12% to 6% for influenza-like illness, 11% to 5% for antimicrobial prescriptions, 6% to 2% for physician visits, 25% to 16% for children with otitis media, 0.7 versus 0.4 days of absenteeism (22, 40). Rates of hospitalization for participants ≥ 65 years and 6 months to 24 months will be much lower, estimated to be between 1.5 per 1000 individuals per season (13, 14). We acknowledge that for this outcome, along with pneumonia and deaths, the sample size may not be sufficient to detect differences. Nevertheless, we anticipate these data will show trends towards differences and the confidence intervals will help establish whether clinically important effects benefits are plausible with the intervention.

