**Coordinating Centre**

(McMaster University)

Manitoba Provincial Centre

(University of Manitoba)

Cypress Health Region

(Saskatchewan)

Alberta Provincial Centre

(University of Calgary)

Five Hills Health Region

(Saskatchewan)

Alberta Provincial Lab

(Calgary)

Saskatchewan Provincial Lab

(Regina)

Cadham Provincial Lab

(Winnipeg)

National Microbiology Laboratory

(Winnipeg, Manitoba)

**Table 1.** Characteristics of eligible Hutterite colonies.

| **CHARACTERISTIC** | **Study provinces** | | | **Total** |
| --- | --- | --- | --- | --- |
|  | **Alb.** | **Sask.** | **Man.** |  |
| Number of colonies | 38 | 17 | 17 | 72 |
| Number of high risk participants | 581 | 306 | 436 | **1323** |
| Number ≥ 65 yrs | 198 | 91 | 86 | 375 |
| Number ≥ 6 mo ≤23 mo | 165 | 96 | 121 | 382 |
| Number with cardiopulmonary conditions | 30 | 9 | 55 | 94 |
| Number with metabolic conditions | 89 | 51 | 46 | 186 |
| Number with neurological conditions | 0 | 3 | 5 | 8 |
| Number with other high risk conditions | 29 | 17 | 90 | 136 |
| Number of healthy children between 36 mo. to 15 yrs | 920 | 430 | 408 | **1758** |
| Number of other colony members | 2005 | 793 | 728 | **3526** |
| Total number of eligible participants | 3506 | 1529 | 1572 | **6607** |

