**Table 2.A. Schedule of active and placebo vaccination for participants < 9 years at year 1***

| Study Year | Influenza Arm | | Hepatitis Arm | | |
| --- | --- | --- | --- | --- | --- |
|  | Week 1 | Week 4 | | Week 1 | Week 4 |
| Year 1 | V | V | | A | S |
| Year 2 | V |  | | A |  |
| Year 3* | V |  | | S |  |

**Table 2.B.** Schedule of active and placebo vaccination for participants ≥ 9 years at year 1*

| Study Year | Influenza Arm | | Hepatitis Arm | | |
| --- | --- | --- | --- | --- | --- |
|  | Week 1 | Week 4 | | Week 1 | Week 4 |
| Year 1 | V |  | | A |  |
| Year 2 | V |  | | A |  |
| Year 3* | V |  | | S |  |

*V denotes VAXIGRIP vaccine, A denoted AVAXIM, S denotes physiologic saline.

* Individuals immunized with AVAXIM for the first time in Year 3 will receive a booster 12 months later after completion of the trial. Individuals who received the first dose of hepatitis the previous year will receive second dose in year 3.

**Table 3.** Power calculations for ICC’s ranging from 0.01 to 0.05, assuming either a 10% or 8% attack rate and relative risk reduction of 50%, two-sided alpha of 0.05, 60 clusters, and cluster size of 50.

| *Control rate* | *Intervention*  *rate* | *Cluster*  *size* | *Colonies*  *Total* | *Participants per group* | *ICC* | *Power* |
| --- | --- | --- | --- | --- | --- | --- |
| 0.10 | 0.05 | 50 | 60 | 1500 | 0.01 | 99% |
| 0.10 | 0.05 | 50 | 60 | 1500 | 0.02 | 96% |
| 0.10 | 0.05 | 50 | 60 | 1500 | 0.03 | 91% |
| 0.10 | 0.05 | 50 | 60 | 1500 | 0.04 | 85% |
| 0.10 | 0.05 | 50 | 60 | 1500 | 0.05 | 80% |
| 0.08 | 0.04 | 50 | 60 | 1500 | 0.01 | 90% |
| 0.08 | 0.04 | 50 | 60 | 1500 | 0.02 | 90% |
| 0.08 | 0.04 | 50 | 60 | 1500 | 0.03 | 83% |
| 0.08 | 0.04 | 50 | 60 | 1500 | 0.04 | 76% |

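### The cluster size of 50 in section 2.11 is not the typical number of people in an interested colony (Table 1: about 92, or about 67 in the primary population); the effect on primary power is small and conservative, but reusing 50 for otitis media overstates power.

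*Protocol*

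**What the plan says.** - Section 2.11 gives the reason for its cluster size: "We have assumed a cluster size of 50, which is the typical number of individuals in colonies interested in participating in the study". With 30 colonies per arm it adds: "This equates to a sample size of 1500 participants in each group".
- The caption of Table 3 repeats the inputs: "relative risk reduction of 50%, two-sided alpha of 0.05, 60 clusters, and cluster size of 50". Printed power for 10% versus 5% runs from 99% at an ICC of 0.01 to 80% at 0.05. For 8% versus 4% it runs from 90% at 0.01 to 76% at 0.04.
- Section 2.11 then uses 50 per cluster, with an ICC of 0.04, to claim at least 90% power for several secondary outcomes. One of them is otitis media in children, 25% versus 16%.
- Table 1 covers the 72 eligible, interested colonies. It lists 1323 high risk members, 1758 healthy children aged 36 months to 15 years, and 3526 in the row "Number of other colony members". The row "Total number of eligible participants" is 6607, the sum of the three.
- Section 1.3.6.1 describes "colonies of typically 80 to 120 people".
- Sections 2.5.2 A and 2.8.1 define the primary population as all members other than the immunized healthy children, so high risk members are included.
- Section 2.14 mentions, in passing, an expected enrolment of 50 per colony. It gives no participation rate and does not say which participants are counted.
- Section 2.9.4 limits the otitis media outcome to children up to 5 years of age.

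**The concern.** The cluster size enters the variance inflation factor, the number per group and every row of Table 3. The reason given for it is a statement of fact about the interested colonies, and the protocol's own census of those colonies does not bear it out. The only Table 1 count near 50 per colony is the residual row of other members, which leaves out the high risk members who belong to the primary population.

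Two things are at stake. A reader cannot tell whether 1500 per group is a count of eligible people or a forecast of enrolment. And a single cluster size is carried over to outcomes assessed in quite different numbers of people, where the error need not be on the safe side.

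**Working it through.** **People per colony (Table 1, 72 colonies)**
- All eligible: 6607/72 = 91.8.
- Primary population: (1323 + 3526)/72 = 4849/72 = 67.3. By province: Alberta 68.1, Saskatchewan 64.6, Manitoba 68.5.
- Other members only: 3526/72 = 49.0. High risk only: 1323/72 = 18.4.
- Section 1.3.7.2 gives 15.5 high risk members per colony. With that figure the primary population is 49.0 + 15.5 = 64.5.
- Participation implied by enrolling 50: 50/67.3 = 74% (50/64.5 = 78%).

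**Method**

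With m people per colony, 30 colonies per arm and intracluster correlation ICC:
- n_eff = 30m / [1 + (m − 1) × ICC]
- SE = √{[p1(1 − p1) + p2(1 − p2)] / n_eff}
- power = Φ(|p1 − p2|/SE − 1.96)

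The t version uses a non-central t with 60 − 2 = 58 degrees of freedom.

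**Reproducing Table 3 at m = 50**

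For 10% versus 5% at ICC 0.04, the inflation factor is 1 + 49 × 0.04 = 2.96 and n_eff = 1500/2.96 = 506.8. SE = √(0.1375/506.8) = 0.01647, and Φ(3.035 − 1.96) = 85.9% (printed 85%).

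The five 10% rows come out at 99.0, 96.0, 91.4, 85.9 and 80.3%, in line with the table. The 8% rows at ICC 0.02 to 0.04 come out at 90.8, 83.8 and 76.8%, also in line. The 8% row at ICC 0.01 does not reproduce (about 96.7%, printed 90%); that is a separate matter, unrelated to cluster size.

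**At the Table 1 size, m = 67.3, full participation**

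Number per group: 30 × 67.35 = about 2020. At ICC 0.04, n_eff = 2020/3.654 = 552.9, SE = 0.01577, and Φ(3.171 − 1.96) = 88.7%.

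| Contrast, ICC | m = 50, normal | m = 67.3, normal | m = 50, t (58 df) | m = 67.3, t (58 df) |
|---|---|---|---|---|
| 10% vs 5%, 0.04 | 85.9% | 88.7% | 84.7% | 87.7% |
| 10% vs 5%, 0.05 | 80.3% | 83.1% | 79.0% | 81.8% |
| 8% vs 4%, 0.04 | 76.8% | 80.3% | 75.4% | 78.9% |

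**Otitis media: 25% versus 16%, ICC 0.04**

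Here p1(1 − p1) + p2(1 − p2) = 0.1875 + 0.1344 = 0.3219. At m = 20, n_eff = 600/1.76 = 340.9, SE = 0.03073, and Φ(2.929 − 1.96) = 83.4%.

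| Children assessed per colony | 10 | 15 | 20 | 24.4 | 50 |
|---|---|---|---|---|---|
| Power (normal) | 65.4% | 76.9% | 83.4% | 87.0% | 94.6% |

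The documents give no count of children up to 5 years, so 10 to 20 is an assumption. Two Table 1 rows roughly bracket it if ages are spread evenly:
- Healthy children aged 36 months to 15 years: 1758/72 = 24.4 over about 12 years, so about 10 in five years.
- Children aged 6 to 23 months: 382/72 = 5.3 over 1.5 years, so about 18 in five years.

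Solving for 90% power needs n_eff = 0.3219 × (3.2415/0.09)² = 417.6, which is m of about 30. Section 1.3.6.2 puts 34% of members at 14 years or younger, about 0.34 × 91.8 = 31 per colony. The claim would therefore need nearly every child up to 14, for an outcome restricted to those up to 5.

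**The case against.** The best defence is that 50 is an enrolment figure. Section 2.14 says so, Table 1 counts eligible people rather than enrolled ones, and 50 enrolled out of 67 eligible is no contradiction. Table 3 declares its cluster size openly and, one row aside, reproduces at that value. All of this stands. What it does not rescue is the reason given in section 2.11, which describes the colonies and not enrolment, or the missing participation rate.

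A reader might infer that the pilot refutes 50, because 74% lies below its 80% and 87%. The documents do not support that. The 80% is for healthy children, who are outside the primary population, and the 87% is for high risk members only. Other members are 3526/4849 = 73% of the primary population, and the pilot reports no participation for them. If 87% of the 18.4 high risk members enrol, reaching 50 needs only (50 − 16.0)/49.0 = 69% of the rest, which nothing in the protocol rules out.

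Nor is 67.3 itself firm, since the 15.5 in section 1.3.7.2 brings it to about 64.5.

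**Conclusion.** The stated justification for the cluster size is wrong as written, and 50 is tenable only as expected enrolment at a participation rate that the protocol leaves unstated.

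For the primary outcome the consequence is minor and in the safe direction: about 3 points of power at ICC 0.04 to 0.05 if every eligible person takes part. If 87% participation is assumed for the whole primary population (m = 67.35 × 0.87 = 58.6) and a t reference is used, power for 10% versus 5% is 86.4% at ICC 0.04 and 80.6% at 0.05. Both are within one point of the 85.9% and 80.3% obtained at m = 50 with a normal reference. A reader might conclude that the trial is underpowered or that Table 3 is invalid. Neither follows: 60 colonies remain adequate on the protocol's own assumptions.

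The reassurance does not extend to every secondary outcome. A reader might apply 92 per colony to all of them because they are described as measured in all participants, but otitis media is not. For that outcome 50 overstates power: about 65% to 83%, on an assumed 10 to 20 children per colony, against 94.6% at 50.

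**What to change.** 1. In section 2.11, replace the statement about the typical number of individuals with the expected enrolment: the Table 1 primary population per colony times a stated participation rate. If 50 is kept as a deliberately cautious enrolment figure, say so and give the roughly 74% that it implies. Use one high risk count per colony (18.4 from Table 1 or 15.5 from section 1.3.7.2).
2. Make the 1500 per group and Table 3 consistent with that value. Preferably use a t reference with 58 df to match the t-test planned in section 2.16; at m = 50, ICC 0.05 and 10% versus 5%, the entry is then 79.0% rather than 80%.
3. For each secondary outcome, use the number per colony in whom it is assessed. Restate the otitis media power from an actual count of children up to 5 years.

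The cost is a recalculation, one count from the demographic survey and revised wording. The number of colonies and the study procedures do not change.

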Viral serotyping

**Figure 6:** Study administration and structure

Data Safety & Monitoring Board

**Coordinating Centre**

(McMaster University)

Manitoba Provincial Centre

(University of Manitoba)

Cypress Health Region

(Saskatchewan)

Alberta Provincial Centre

(University of Calgary)

Five Hills Health Region

(Saskatchewan)

Alberta Provincial Lab

(Calgary)

Saskatchewan Provincial Lab

(Regina)

Cadham Provincial Lab

(Winnipeg)

National Microbiology Laboratory

(Winnipeg, Manitoba)

**Table 1.** Characteristics of eligible Hutterite colonies.

| **CHARACTERISTIC** | **Study provinces** | | | **Total** |
| --- | --- | --- | --- | --- |
|  | **Alb.** | **Sask.** | **Man.** |  |
| Number of colonies | 38 | 17 | 17 | 72 |
| Number of high risk participants | 581 | 306 | 436 | **1323** |
| Number ≥ 65 yrs | 198 | 91 | 86 | 375 |
| Number ≥ 6 mo ≤23 mo | 165 | 96 | 121 | 382 |
| Number with cardiopulmonary conditions | 30 | 9 | 55 | 94 |
| Number with metabolic conditions | 89 | 51 | 46 | 186 |
| Number with neurological conditions | 0 | 3 | 5 | 8 |
| Number with other high risk conditions | 29 | 17 | 90 | 136 |
| Number of healthy children between 36 mo. to 15 yrs | 920 | 430 | 408 | **1758** |
| Number of other colony members | 2005 | 793 | 728 | **3526** |
| Total number of eligible participants | 3506 | 1529 | 1572 | **6607** |

**Table 2.A. Schedule of active and placebo vaccination for participants < 9 years at year 1***

| Study Year | Influenza Arm | | Hepatitis Arm | | |
| --- | --- | --- | --- | --- | --- |
|  | Week 1 | Week 4 | | Week 1 | Week 4 |
| Year 1 | V | V | | A | S |
| Year 2 | V |  | | A |  |
| Year 3* | V |  | | S |  |

**Table 2.B.** Schedule of active and placebo vaccination for participants ≥ 9 years at year 1*

| Study Year | Influenza Arm | | Hepatitis Arm | | |
| --- | --- | --- | --- | --- | --- |
|  | Week 1 | Week 4 | | Week 1 | Week 4 |
| Year 1 | V |  | | A |  |
| Year 2 | V |  | | A |  |
| Year 3* | V |  | | S |  |

*V denotes VAXIGRIP vaccine, A denoted AVAXIM, S denotes physiologic saline.

* Individuals immunized with AVAXIM for the first time in Year 3 will receive a booster 12 months later after completion of the trial. Individuals who received the first dose of hepatitis the previous year will receive second dose in year 3.

**Table 3.** Power calculations for ICC’s ranging from 0.01 to 0.05, assuming either a 10% or 8% attack rate and relative risk reduction of 50%, two-sided alpha of 0.05, 60 clusters, and cluster size of 50.

| *Control rate* | *Intervention*  *rate* | *Cluster*  *size* | *Colonies*  *Total* | *Participants per group* | *ICC* | *Power* |
| --- | --- | --- | --- | --- | --- | --- |
| 0.10 | 0.05 | 50 | 60 | 1500 | 0.01 | 99% |
| 0.10 | 0.05 | 50 | 60 | 1500 | 0.02 | 96% |
| 0.10 | 0.05 | 50 | 60 | 1500 | 0.03 | 91% |
| 0.10 | 0.05 | 50 | 60 | 1500 | 0.04 | 85% |
| 0.10 | 0.05 | 50 | 60 | 1500 | 0.05 | 80% |
| 0.08 | 0.04 | 50 | 60 | 1500 | 0.01 | 90% |
| 0.08 | 0.04 | 50 | 60 | 1500 | 0.02 | 90% |
| 0.08 | 0.04 | 50 | 60 | 1500 | 0.03 | 83% |
| 0.08 | 0.04 | 50 | 60 | 1500 | 0.04 | 76% |

**Table 4: Study calendar**

| **Activities** | **08/2008-07/2009** | | | | | | **08/2009-07/2010** | | | | | | **08/2010-07/2011** | | | | | |
| --- | --- | --- | --- | --- | --- | --- | --- | --- | --- | --- | --- | --- | --- | --- | --- | --- | --- | --- |
| 08 09 | 11 | 01 | 03 | 05 | 07 | 08 09 | 11 | 01 | 03 | 05 | 07 | 08 09 | 11 | 01 | 03 | 05 | 07 |
| Training of nurses |  |  |  |  |  |  |  |  |  |  |  |  |  |  |  |  |  |  |
| Allocation of intervention |  |  |  |  |  |  |  |  |  |  |  |  |  |  |  |  |  |  |
| Enrolling healthy children |  |  |  |  |  |  |  |  |  |  |  |  |  |  |  |  |  |  |
| Enrolling other participants |  |  |  |  |  |  |  |  |  |  |  |  |  |  |  |  |  |  |
| Pre season serology |  |  |  |  |  |  |  |  |  |  |  |  |  |  |  |  |  |  |
| Vaccination of children |  |  |  |  |  |  |  |  |  |  |  |  |  |  |  |  |  |  |
| Post vaccine serology |  |  |  |  |  |  |  | ß |  |  |  |  |  |  * |  |  |  |  |
| Follow-up** † |  |  |  |  |  |  |  |  |  |  |  |  |  |  |  |  |  |  |
| Mid season  serology |  |  |  |  |  |  |  |  |  |  |  |  |  |  |  |  |  |  |
| Post season serology* |  |  |  |  |  |  |  |  |  |  |  |  |  |  |  |  |  |  |
| Data Collection |  |  |  |  |  |  |  |  |  |  |  |  |  |  |  |  |  |  |
| Yearly reports to DSMB |  |  |  |  |  |  |  |  |  |  |  |  |  |  |  |  |  |  |
| End of Season report |  |  |  |  |  |  |  |  |  |  |  |  |  |  |  |  |  |  |
| Data analysis |  |  |  |  |  |  |  |  |  |  |  |  |  |  |  |  |  |  |
| Manuscript preparation |  |  |  |  |  |  |  |  |  |  |  |  |  |  |  |  |  |  |

*Second and third year blood will be collected from the vaccine group to confirm children receiving hepatitis A have developed protective titres.

**Follow-up and post-season serology dates will be determined by the influenza activity within the health region.

†- Acute and convalescent blood samples will be collected from health vaccinated children as required.

**Table 5:** Schedule of events and study forms

| **Data Collected, or Event** | **Enrolment**  **& first blood draw** | **Vaccination** | **Post-Vaccination**  Vaccination + 3 d | **Second Vaccination & blood draw**  Vaccination + 1 mo | **Follow-up Visits**  Start to end of influenza season (2xs/wk) | **Mid-Season Blood Draw** | **Final blood draw**  End of Influenza season |
| --- | --- | --- | --- | --- | --- | --- | --- |
| Informed Consent | X |  |  |  |  |  |  |
| Screening and Enrolment Log  (Form 00) | X |  |  |  |  |  |  |
| Influenza Visit Log  (Form 01) | X | X | X | X | X | X | X |
| Eligibility Form (Form 10) | X |  |  |  |  |  |  |
| Blood draw for HI | X  HR |  |  | X  HR* Yr 2 & 3 VG |  | X  HR | X  HR |
| Influenza Serology Log  (Form 02) | X  HR |  |  | X  HR* VG |  | X  HR | X  HR |
| Vaccination Questionnaire  (Form 20) |  | X  VG |  | X  VG (<9**) |  |  |  |
| Vaccination |  | X  VG |  | X  VG (<9**) |  |  |  |
| Vaccination Log  (Form 03) |  | X  VG |  | X  VG (<9**) |  |  |  |
| Post-Vaccination Form  (Form 21) |  |  | X  VG |  |  |  |  |
| Serious Adverse Event Reporting Form (Form 22) |  | As needed  VG | As needed  VG | As needed  VG (<9**) |  |  |  |
| Adverse Event Observation Form  (Form 23) |  | As needed  VG | As needed  VG | As needed  VG |  |  |  |
| Follow-up Form  (Form 30) |  |  |  |  | X  ALL GROUPS |  |  |
| Respiratory Infection Form  (Form 31) |  |  |  |  | As needed  ALL GROUPS |  |  |
| Nasopharyngeal Swab/Throat Swab |  |  |  |  | As needed  ALL GROUPS |  |  |
| Nasopharyngeal Swab Log  (Form 04) |  |  |  |  | As needed  ALL GROUPS |  |  |
| Acute and convalescent serology |  |  |  |  | As needed  VG |  |  |
| Primary Care Data Collection Form (Form 40) |  |  |  |  | As needed  ALL GROUPS |  |  |
| Hospitalization Data Collection Form (Form 41) |  |  |  |  | As needed  ALL GROUPS |  |  |
| Discontinuation Report  (Form 50) |  | As needed | As needed | As needed | As needed | As needed | As needed |

ALL GROUPS= VG (vaccination group) and OH (other group), including HR (high risk group- other sub group)

* HR individuals who have received a flu shot, ** Individuals in the vaccination group who are < 9 years old and have not had a previous flu shot
